### Patients’ assessments of dressing wear time

On their return in the second week after operation, patients will be asked to rate their dressing wear time with regard to safety, comfort and convenience, by the use of a 5-point rating scale (Table 
2)
[35].

**Table 2 T2:** Patients’ self-assessment of dressing wear time

Please rate the **dressing wear time** following your breast surgery in regard to:				
**Safety**				
( ) Excellent	( ) Very good	( ) Good	( ) Fair	( ) Poor
**Comfort**				
( ) Excellent	( ) Very good	( ) Good	( ) Fair	( ) Poor
**Convenience**				
( ) Excellent	( ) Very good	( ) Good	( ) Fair	( ) Poor
Regardless of how many time your dressing was left in place, **if you had the choice**, would you prefer to keep the dressing for one day or for six days?				
( ) 1 day		( ) 6 days		

### Outcomes measures

The primary outcome is the incidence of SSI, which will be defined on the basis of CDC’s definitions
[39]. Skin colonization rates and patients’ preferences regarding dressing wear time are secondary outcomes.

### End points

Participation is considered complete after the 30^th^ postoperative assessment day if no implants have been used, or after the 12^th^ postoperative month if an implant was used. Another exit point is if the dressings of group II patients get wet before the sixth postoperative day, thus requiring withdrawal from the study.

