## Background

Surgical site infection (SSI) is a relevant problem in surgical practice, with surrounding issues that still need to be clarified
[1-4]. Interventions to reduce the incidence of SSI are essential to reduce not only morbidity, but also costs to the individual and to society
[2,5-7].

The infection risk for clean wounds is estimated to be 1 to 2%
[8]. However, SSI rates following breast surgery seem to be much higher than that expected for clean surgical procedures and range from 1 to 30% in the literature
[7,9-11]. Furthermore, SSI rates after breast cancer surgical procedures are more common than SSI after non-cancer-related breast operations
[7]. The incidence in the literature of SSI after mastectomy varies from 1% to 28%
[5,12-14], and SSI rates after breast reconstructive procedures range from 6.3% to 28%
[5,7,15-18].

Identifying SSI risk factors for breast surgery is essential in order to develop infection-prevention strategies and improve surgical outcomes
[7]. Risk factors for SSI are usually classified into preoperative (patient-related, for example, age, obesity, tobacco use, comorbidities, use of immunosuppressive medications), perioperative (procedure-related factors, such as type and duration of the operation, hypoxia, operating room traffic and operating room parameters) and postoperative categories
[2,19]. One of the major risk factors in the postoperative period is wound management
[2,19-21]. Despite the importance of surgical wound management in preventing infection, literature on incisional wound management is sparse
[21,22].

Postoperative wound care is an ancient practice, with recorded evidence dating back 4,000 years
[23]. Purposes for wound dressing include protection of the wound from trauma and contamination, absorption of wound exudates and compression to minimize edema and obliterate dead space
[23-27].

The search for an ideal postsurgical breast dressing has led to the development of several different materials and application techniques
[28,29]. Despite the abundance of wound dressing products available nowadays, there is little empiric evidence to guide product choice for site-specific incisional wounds
[26,30], and traditional low-technology gauze-based dressings are commonly used
[25,27,29,31,32]. Due to lower costs, this kind of dressing is largely used in the public health system in Brazil.

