#### Exclusion criteria

Patients with body mass index (BMI) above 35Kg/m^2^, those with usual contraindications for breast reconstruction procedures, such as diabetes or heavy smoking, will be excluded. Patients whose dressings get wet in the first 24 hours after operation, thus requiring their change, will also be excluded.

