### Groups’ assignment, randomization and allocation concealment

Two hundred patients will be prospectively enrolled after giving informed consent. Patients will be randomly assigned to group I (n = 100), which will have dressings removed on the first postoperative day or to group II (n = 100), whose dressings will be removed on the sixth postoperative day. The rationale for comparing 24 hours versus 144 hours of dressing include CDC recommendation of protecting an incision with a sterile dressing for 24 to 48 hours
[19] (group I) and the time of removing sutures (group II).

The allocation will be determined by a computer-generated sequence (Bioestat 5.0, Instituto de Desenvolvimento Sustentável Mamirauá, Belém, PA, Brazil). A numbered and sealed opaque envelope will be opened on the first postoperative day to reveal the group to which the patient is allocated.

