### Baseline procedures and interventions

Patients will take a shower with liquid detergent-based chlorhexidine 4% prior to the operation
[36], and an alcoholic solution of chlorhexidine 0.5% will be used for the antisepsis of the surgical site in the operating room
[37]. Patients will undergo immediate or delayed breast reconstruction under general anesthesia, by the use of flaps and/or implants and, performed by the same surgical team. All patients will receive prophylactic antibiotics (cephazolin).

At the end of the operation, the surgical site will be cleansed with sterile physiological saline, a sample for quantitative skin culture will be obtained and a conventional gauze and tape dressing, which use is the established practice in our hospital, will be applied. Sutured wounds will be completely covered with four layers of dry sterile cotton gauze and fixed in place by a microporous adhesive tape. The surgical team will not be aware of the group to which the patient will be allocated.

Patients allocated to group I will be instructed to keep their wounds uncovered and to follow their usual personal hygiene routine, and patients in group II will be instructed not to wet the dressing.

Quantitative skin cultures will be obtained in the operating room immediately before applying the dressing, as well as immediately after the removal of dressing. In group I, an additional sample will be collected at the sixth postoperative day. A standard 5cm by 10 cm area (determined by a sterile pattern) over the surgical wound will be swabbed with a sterile cotton swab pre-moistened with sterile saline. This swab will be placed in a sterile container with 1.0 ml of saline and immediately conducted to the laboratory.

Patients will be discharged from the hospital on the first postoperative day after allocation, and they will return weekly for follow-up, for four weeks.

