### Assessment of postoperative infection

The Centers for Disease Control and Prevention (CDC) considers SSI to be an infection that occurs within 30 days after the operative procedure if no implant is left in place, or within one year if an implant is in place and the infection appears to be related to the operative procedure
[39]. Thus, patients will be systematically followed-up once a week for 30 days regarding postoperative infection, by a single surgeon. Patients who receive an implant will have an additional assessment by the same surgeon, one year after the operation. The CDC definitions and classifications of SSI will be considered (Table 
1)
[39]. As with all CDC definitions of nosocomial infections, a surgeon’s diagnosis of infection will be considered an acceptable criterion for an SSI
[39].

**Table 1 T1:** **CDC definitions of SSI**[39]

**Superficial incisional SSI**	**Deep incisional SSI**	**Organ/Space SSI**
Involves only skin or subcutaneous tissue and meets at least one of the following:	Involves deep soft tissues (fascial and muscle layers) and meets at least one of the following:	Involves any part of the anatomy (organs or spaces) and meets at least one of the following:
• Purulent drainage from the superficial incision;	• Purulent drainage from the deep incision but not from the organ/space component of the surgical site;	• Purulent drainage from a drain that is placed through a stab wound into the organ/space;
• Organisms isolated from an aseptically obtained culture of fluid or tissue from the superficial incision;	• A deep incision that spontaneously dehisces or is deliberately opened by a surgeon when the patient has at least one of the following signs or symptoms: fever (>38°C), localized pain or tenderness, unless the incision is culture-negative;	• Organisms isolated from an aseptically obtained culture of fluid or tissue in the organ/space;
• At least one of the following signs or symptoms of infection: pain or tenderness, localized swelling, redness or heat, and the superficial incision is deliberately opened by surgeon unless the incision is culture-negative;	• An abscess or other evidence of infection involving the deep incision is found on direct examination, during reoperation, or by histopathologic or radiologic examination;	• An abscess or other evidence of infection involving the organ/space that is found on direct examination, during reoperation, or by histopathologic or radiologic examination;

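### Withdrawing only group II patients when a dressing gets wet, after allocation, can bias the primary SSI comparison by an unknown amount and in an unknown direction

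*Protocol article*

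**What the plan says.** Under the randomisation heading, the protocol article says "A numbered and sealed opaque envelope will be opened on the first postoperative day to reveal the group to which the patient is allocated". From then on the arms differ. Under Baseline procedures and interventions, "Patients allocated to group I will be instructed to keep their wounds uncovered and to follow their usual personal hygiene routine", while "patients in group II will be instructed not to wet the dressing".

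The End points section first defines when participation is complete: day 30, or month 12 if an implant was used. It then adds a second way out: "Another exit point is if the dressings of group II patients get wet before the sixth postoperative day, thus requiring withdrawal from the study". No matching exit is given for group I.

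A separate rule under Exclusion criteria covers the earlier period and names no arm: "Patients whose dressings get wet in the first 24 hours after operation, thus requiring their change, will also be excluded".

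SSI by CDC definitions is the primary outcome. It is assessed weekly for 30 days, with a further assessment at one year for implant patients, and is compared between groups by the Fisher test.

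**The concern.** Randomisation protects the comparison only while the patients compared are those who were randomised. This rule removes patients after allocation, from one arm, for an event that only that arm's assigned strategy makes possible.

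The event may also carry information about the outcome. The rule does not separate water from outside from fluid from the wound. The Background lists among the purposes of a dressing "absorption of wound exudates and compression to minimize edema and obliterate dead space", and Table 1 counts "Purulent drainage from the superficial incision" as sufficient for a superficial SSI. A dressing soaked from beneath could therefore be an early sign of the primary event, or the event itself.

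Because the rule ends participation, the harm comes at data collection. An intention-to-treat statement in an analysis plan that is not shown could not restore outcomes that were never recorded. The trial is meant to support recommendations on wear time, so its primary comparison is at stake.

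**Working it through.** **Timing and arms.** The envelope is opened on day one and the exit runs to day six, so the trigger falls after allocation. Group I has no dressing in that window. The selection is therefore one-sided, whatever the figures below show.

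**Inputs from the article.** 100 patients per arm; two-group Fisher test at 5% (taken here as two-sided); relevant difference 10%, read as percentage points; SSI after reconstruction 6.3% to 28% (Background). The 100 per arm cannot be reproduced from the article's inputs alone, because no single baseline rate is stated. Nothing below depends on reproducing it.

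**Assumed inputs, not in the article.** w is the share of group II withdrawn, and RR is the SSI risk of patients whose dressing gets wet relative to those whose dressing stays dry.

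**Formula.** If the whole of group II has risk r and the dry patients have risk d, then r = (1 − w)·d + w·RR·d. The rate seen in those retained is d = r / (1 − w + w·RR).

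**No true difference, 10% in both arms:**

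| w | RR | Retained group II rate | Bias (points) | Fisher type I error |
|---|---|---|---|---|
| 0 | – | 10% | 0 | 2.9% |
| 10% | 1 | 0.10/1.00 = 10% | 0 | 3.6% |
| 5% | 2 | 0.10/1.05 = 9.5% | −0.5 | 3.9% |
| 10% | 3 | 0.10/1.20 = 8.3% | −1.7 | 4.9% |
| 20% | 3 | 0.10/1.40 = 7.1% | −2.9 | 8.3% |

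Type I error is by exact enumeration of the two-sided Fisher test, with 100 in group I and 100·(1 − w) in group II. Of the 8.3%, 8.0 points wrongly favour group II. The row at RR 1 shows that part of the rise comes only from the changed group size, because the Fisher test is conservative at 100 against 100.

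**Sign.** If wet patients had half the risk of dry ones (RR 0.5, w 20%), the retained rate would be 0.10/(0.80 + 0.10) = 11.1%, and the bias would run the other way.

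**Across the article's SSI range, at w 20% and RR 3.** At 6.3%: 0.063/1.40 = 4.5%, a bias of 1.8 points. At 28%: 0.28/1.40 = 20%, a bias of 8.0 points, with type I error 20.9%.

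**If longer wear were truly worse, 10% against 20%.** With RR 3, the retained group II rate is 0.20/1.20 = 16.7% at w 10%, and 0.20/1.40 = 14.3% at w 20%. The difference of 10 points shrinks to 6.7 and 4.3. Exact Fisher power falls from 0.44 to 0.24 and 0.12. With RR 1 it stays at 0.46 and 0.44.

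**The case against.** The best defence is that the only cause of wetting the article addresses after day one is patient behaviour. If dressings get wet mainly through accidental bathing, RR may be close to 1 and the bias close to zero. No wetting rate is given, and the larger effects need both many withdrawals and a strong link with infection. At 10% SSI, the settings with 5% withdrawn at RR 2, or 10% at RR 3, leave the type I error below the nominal 5%. All of this stands, and it limits what can be said about size and direction. It does not make the rule harmless: nothing in the article shows that wetting is unrelated to SSI, and the outcomes that would show it are the ones lost.

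Four stronger readings are tempting, and the documents do not support them:

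- **That the bias is known to favour longer wear.** This needs a higher SSI risk in wet patients, which no section states.
- **That wetting is the main way in which longer wear fails.** Nothing in the article says so.
- **That the 24-hour exclusion is also one-sided.** It names no arm, and the article describes the contrast as 24 against 144 hours of dressing, so both groups wear one in that period. To make it one-sided, one must suppose that envelopes are opened before 24 hours have passed.
- **That 100 per arm is faulty for lack of an attrition allowance.** A condensed article may leave this to the full protocol. The same holds for the analysis population, which an analysis plan may name.

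**Conclusion.** The point holds in a conditional form. The withdrawal rule is arm-specific, acts after allocation and ends outcome collection, so following it as written replaces the randomised comparison with all of group I against a selected part of group II. That much rests on the text alone and is certain.

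The size and sign of the resulting bias are unknown. A bias towards longer wear is the more plausible direction if wetting reflects exudate or drainage. Under the assumed inputs at 10% SSI with no true effect, it runs from nothing (RR 1) to about 3 points (20% withdrawn, RR 3), and it is larger at higher SSI rates. These figures illustrate what the rule could do; they do not estimate what it has done. Because the rule acts on the primary outcome and lost outcomes may not be recoverable, it should be changed before further patients are withdrawn.

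**What to change.** Amend the End points section:

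1. Replace withdrawal from the study with recording the wet dressing, its date and, where known, its source as a protocol deviation.
2. Keep the patient in the scheduled SSI follow-up: weekly to day 30, and at one year for implant patients.
3. State that every patient whose envelope was opened is analysed in the allocated group for the primary Fisher comparison.
4. Keep the group II patients whose dressing stayed dry to day six as a per-protocol sensitivity analysis against group I.
5. For any group II patients already withdrawn (134 patients had been operated on by the end of December 2012; the article does not say whether any were withdrawn), seek the SSI outcome from records where available, and report how many could not be recovered.

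The cost is a short amendment, follow-up visits for patients who would otherwise have left, and a record review that may be incomplete, since those records may lack the weekly single-surgeon assessments. The primary analysis will contain some patients without the full six-day exposure, which dilutes the contrast a little; the per-protocol analysis addresses that. How a wet dressing is managed clinically stays with the trial team. The change concerns only follow-up and analysis.

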### Statistical analysis

The rejection level for the null hypothesis will be fixed at 5% (α ≤ 0.05). The Mann-Whitney test will be used to compare groups I and II with regard to age, BMI and duration of operation.

The Fisher test will be used to compare groups I and II regarding SSI occurrence. Logistic regressions will be applied to detect significant associations between variables such as age, BMI and duration of operation and the incidence of SSI.

For inter-group assessment of skin colonization, the Mann-Whitney test will be used to compare groups I and II pre-dressing and at the sixth postoperative day. These tests will be applied independently for each medium used. Because skin colonization could play a role in SSI rates, an intra-group assessment of skin colonization will also be performed. For this assessment, in group I Friedman two-way analysis of variance will be used to assess the differences in number of CFU among the three moments (pre-dressing, first and sixth postoperative day). Whenever the difference is significant, the Friedman two-way analysis of variance will be complemented by the multiple comparisons test to determine which moment significantly differed from the others. In group II, the Wilcoxon test will be used to compare the number of CFU pre-dressing and at the sixth postoperative day.

The Kolgomorov-Smirnov test will be applied to compare the two groups regarding patients’ assessments of safety, comfort and convenience. The Fisher test will be used to compare groups I and II regarding patients’ choice (one day or six days).

Statistical analysis will be performed using SPSS (Statistical Package for Social Sciences, Inc., Chicago, IL, USA) v.18 and Bioestat 5.0 (Instituto de Desenvolvimento Sustentável Mamirauá, Belém, PA, Brazil).

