### Sample size

SSI rates following breast reconstruction vary in the literature, from 1% a 30%
[1,4,5,9-11]. We considered clinically relevant a 10% difference in SSI rate
[35]. Specifying an acceptable Type 1 error of 5%, and Type 2 error of 20%, the estimated sample size was 100 patients per arm.

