## Discussion

SSI is a major source of adverse events in patients undergoing breast cancer surgical procedures, generating psychological issues, increased duration of hospitalization and costs, as well as delay in commencing postoperative adjuvant therapies
[2,5,11]. Consequently, surgeons should make a determined effort to prevent SSI. As protocols and guidelines should be founded on evidence-based medicine principles, well-designed studies are essential to support or to adjust clinical practice
[20].

Wound management is a key area in preventing SSI
[21]. However, few studies have focused on the management of the wound after closure as a method of reducing infection
[34]. This randomized trial focuses on the influence of dressing wear time in SSI rates. Since the greater the degree of surgical wound contamination, the higher the risk for infection
[2,19], skin colonization assessment is a secondary aim of this study.

The management of surgical wounds should involve the principle of minimizing harm, and patient preference and tolerance must also be considered
[30]. Thus, assessment of patients’ perceptions of dressing wear time is another secondary aim in this trial. Some authors pointed out that omitting a dressing after the first 24 postoperative hours could be convenient for patients, allowing them to carry out their personal hygiene more easily
[24]. However, other authors observed that dressings are comforting to patients by masking their scars without increasing SSI rates
[23,26,35]. Considering the mutilating characteristics of breast cancer treatment, we hypothesize that patients, particularly those who undergo immediate breast reconstruction, might prefer to keep their dressings in place for a longer time, thus delaying the moment of seeing their reconstructed breasts.

CDC’s guidelines for managing surgical wounds that are closed primarily instruct patients to keep their wounds dry and covered for 24 to 48 hours
[19], but the ideal dressing wear time following breast surgery remains an unsolved issue. The results of this trial may support standard recommendations regarding dressing wear time after breast reconstruction.

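### The primary Fisher test is valid but conservative at 100 per arm; Boschloo's test, a risk difference with its interval, and a group term in the logistic model would use the same data better

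*Protocol article*

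**What the plan says.** Under Statistical analysis, the protocol article fixes the primary comparison: "The Fisher test will be used to compare groups I and II regarding SSI occurrence". The threshold is given in the same section: "The rejection level for the null hypothesis will be fixed at 5" per cent. Whether the test is one- or two-sided is not stated.

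The covariates have a separate role: "Logistic regressions will be applied to detect significant associations between variables such as age, BMI and duration of operation and the incidence of SSI". Allocated group is not named there, though the list of variables is open.

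The benchmark is in Sample size: "We considered clinically relevant a 10% difference in SSI rate". The number of patients follows from it: "Specifying an acceptable Type 1 error of 5%, and Type 2 error of 20%, the estimated sample size was 100 patients per arm". No base rate is fixed. That section cites a literature range of 1% to 30%, and Background gives 6.3% to 28% for reconstructive procedures.

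The Discussion states the ambition: "The results of this trial may support standard recommendations regarding dressing wear time after breast reconstruction".

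**The concern.** Fisher's test conditions on the total number of infections. With few events it has few attainable p-values, so its true size falls well below the nominal 5%. The unused error is lost power, in a trial that reaches its planned 80% only if infection is rarer than its own Background suggests for reconstruction.

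Two further points follow from the same section. First, a non-significant p-value does not show whether the difference called clinically relevant has been excluded, and a recommendation on wear time would turn on that. Second, age, body mass index and operation duration are all known when the envelope is opened on the first postoperative day. They could therefore support an adjusted group comparison, but their stated use is to detect associations with SSI.

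**Working it through.** **Inputs.** 100 per arm, type I error 5%, power 80% and a 10% difference (Sample size; read as percentage points); Fisher test (Statistical analysis). Two-sided testing is an assumption. So is each base rate, because none is fixed.

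**The plan's own figure.** n per arm = [1.96·√(2p̄(1−p̄)) + 0.8416·√(p₁(1−p₁)+p₂(1−p₂))]² / (p₁−p₂)².
- 2% vs 12%: (1.96·√0.1302 + 0.8416·√0.1252)² / 0.01 = (0.707 + 0.298)² / 0.01 ≈ 101.01, rounded up to 102. This is close to the stated 100.
- 6.3% vs 16.3% needs 157, 10% vs 20% needs 199, and 18% vs 28% needs 277.

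So 100 per arm matches a two-sided, uncorrected calculation only near 2% vs 12%.

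**Fisher and Boschloo, by exact enumeration of all 101 × 101 tables.** Size and power are the summed binomial probabilities of the rejected tables. Fisher rejects at p ≤ 0.05. Boschloo's test uses the Fisher p-value as its statistic and rejects up to the largest cutoff whose size, maximised over the common infection rate, stays at or below 0.05. For 100 vs 100 that cutoff is about 0.0638, with maximum size 0.0496.

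| Rates | Fisher size at the lower rate | Fisher power | Boschloo power | Gain |
|---|---|---|---|---|
| 5% vs 15% | 2.1% | 0.586 | 0.630 | 0.044 |
| 6.3% vs 16.3% | 2.5% | 0.538 | 0.582 | 0.044 |
| 10% vs 20% | 2.9% | 0.444 | 0.479 | 0.035 |
| 20% vs 30% | 3.3% | 0.313 | 0.358 | 0.045 |

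The uncorrected chi-square has more power (0.518 at 10% vs 20%), but its size there is 5.2%. The gain available while the level is guaranteed is therefore the 3 to 5 points from Boschloo.

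**Reading a null result.** Wald 95% interval for the risk difference: d ± 1.96·√(p₁(1−p₁)/100 + p₂(1−p₂)/100).
- 10 vs 10 events: 0 ± 1.96·√(0.0009 + 0.0009) = −8.3 to +8.3 points, p = 1.0. Ten points are excluded.
- 12 vs 10 events: 2 points, ± 1.96·√(0.001056 + 0.0009) = −6.7 to +10.7 points, p = 0.82. Ten points are not excluded.
- 10 vs 5 events: 5 points, ± 1.96·√(0.0009 + 0.000475) = −2.3 to +12.3 points, p = 0.28. Ten points are not excluded.

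With equal observed rates the half-width is 1.96·√(2p(1−p)/100): 8.3 points at 10%, 9.9 at 15% and 11.1 at 20%.

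**Covariate adjustment.** The documents give no covariate strengths, so these were assumed: three covariates, each with the same odds ratio per standard deviation, and 2,000 simulated trials per setting (Monte Carlo standard error about 0.011). Against an unadjusted likelihood-ratio test, adjustment added 0 to 1 point of power at an odds ratio of 1.3, about 1 to 4 points at 1.5 and about 4 to 8 points at 2.0. The size of the adjusted test reached 0.062 in some settings, which is a reason to keep it supportive. Expected events are few: 2 + 12 = 14 at 2% vs 12%, and 6.3 + 16.3 ≈ 23 at 6.3% vs 16.3%.

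**The case against.** Fisher's test is prespecified and controls the type I error, and conservatism is not an error. This stands. The case for Boschloo's test is that it is at least as powerful at the same guaranteed level, not that Fisher's is wrong. The gain is modest, and power stays at 0.630, 0.479 and 0.358 in the three main scenarios. The unfixed base rate is the larger power problem, and it is a separate one.

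A reader might infer that the trial will report only a p-value, or that a null result could not be interpreted. The document supports neither. It does not say that estimates will be withheld, and a condensed article may leave intervals to the full protocol or analysis plan. The outcome is binary in two arms, so the counts give the risk difference and its interval directly. With 10 vs 10 events, 10 points would be excluded.

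A reader might also infer that leaving out adjustment costs substantial power or biases the comparison. No stratification factor is stated, so the unadjusted comparison is valid. The gain from adjustment depends on assumed covariate strengths, and the open list of variables does not rule out group as a term.

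Finally, it is tempting to require the interval to lie within ±10 points before claiming no relevant influence. The protocol sets a difference to detect, not an equivalence margin, so this would be a new objective. It would also be poorly powered: with truly equal rates, a 95% Newcombe interval would lie inside ±10 points with probability 66% at 5% SSI, 25% at 10%, 5% at 15% and 0.2% at 20%.

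**Conclusion.** The point holds as an available improvement, not as an error in the plan. At 100 per arm, two-sided, Fisher's test uses only about 2.1% to 3.3% of its 5% at SSI rates of 5% to 20%. Boschloo's test recovers about 3 to 5 points of power with the level still at or below 5%. Those figures assume that all 100 patients per arm are analysed, and the power figures also take a 10-point difference.

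The benefit of a group term in the logistic model is unknown in size and probably small. The risk difference and its interval matter for interpretation: 12 vs 10 events gives p = 0.82 and still leaves 10 points inside the interval. None of these changes brings power back to 80% at the reconstruction rates quoted in Background.

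**What to change.** Fix the following in writing before any comparison by arm:

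1. Replace Fisher's test for SSI by Boschloo's unconditional exact test, two-sided at 5%.
2. Report beside it the SSI risk difference, group I minus group II, with a 95% Newcombe or Miettinen-Nurminen interval. State that a non-significant result will be read against the 10-point difference in Sample size. Add no formal equivalence rule.
3. Name allocated group as a term in the planned logistic model, with a short prespecified covariate list (age, body mass index, operation duration) and a Firth penalty because events are few. Label this analysis supportive.

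The cost is analysis wording only: no more patients, visits or data. Boschloo's test and the Firth penalty may need software beyond the two packages named (SPSS v.18 and Bioestat 5.0), for example R or Python. Trial status reports recruitment as still open, with 134 patients operated on by the end of December 2012, so at that point the change could still be made.

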### Microbiological methods

Standard microbiological methods and criteria will be used to identify microorganisms
[38]. Aliquots of 0.2 ml of the sample will be plated on hypertonic manitol (HM) agar, selective for staphylococci; on blood agar, to identify hemolytic colonies; on Sabouraud agar with chloramphenicol (0.05mg/ml), selective for fungi and yeasts; and on eosin-methylene blue (EMB) agar, selective for enterobacteria. The plates will be incubated aerobically for 48 hours at 37°C. The same laboratory technician will process all samples and, after 48 hours, the plates will be examined by a microbiologist.

Bacterial count results will be reported as colony forming units (CFU) per plate. Whenever CFU count in a plate exceeds 300, it will be scored as over 300. Staphylococci will be identified as coagulase-negative *Staphylococcus* sp. or *S. aureus* on the basis of Gram stain, the presence of hemolysis and on coagulase testing. The same microbiologist will assess all the plates. Both the laboratory technician and the microbiologist will be blinded.

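### The day-6 skin-colonisation comparison is valid but leaves the pre-dressing count unused except in a baseline significance test; adjusting for it is a free, minor improvement

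*Protocol article*

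**What the plan says.** All references are to the protocol article.

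- **Sampling** (Baseline procedures and interventions): "Quantitative skin cultures will be obtained in the operating room immediately before applying the dressing". A second swab follows removal of the dressing, on day 1 in group I and day 6 in group II. Group I has a further swab on day 6, so group I gives three samples and group II two.
- **Allocation** (Groups' assignment, randomization and allocation concealment): the sealed envelope is opened on the first postoperative day, after the pre-dressing swab.
- **Counts** (Microbiological methods): four media are plated. "Whenever CFU count in a plate exceeds 300, it will be scored as over 300".
- **Between-arm analysis** (Statistical analysis): "the Mann-Whitney test will be used to compare groups I and II pre-dressing and at the sixth postoperative day", separately for each medium. No listed analysis uses the pre-dressing count as a covariate or compares change between arms.
- **Within-arm analysis** (Statistical analysis): "an intra-group assessment of skin colonization will also be performed", by Friedman over three times in group I and Wilcoxon over two in group II. The reason given is that colonisation might contribute to infection.
- **Status** (Study aims; Outcomes measures): the influence of wear time on colonisation is a secondary aim and colonisation a secondary outcome.

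**The concern.** The pre-dressing count is a baseline measured on the same media as the outcome, in every patient, before anyone knows the arm. The plan uses it between arms only in a significance test. Wear time cannot have affected that count, so the test answers no question about wear time, and the plan attaches no consequence to its result. The day-6 comparison then takes no account of where each patient started.

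At stake are precision for a secondary aim and protection against a day-6 difference that merely carries forward a chance difference at baseline. A lesser matter is interpretation: with a test of change reported separately for each arm, a reader may contrast the two p-values and take the contrast as evidence on wear time.

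**Working it through.** **Inputs.** From the article: 100 patients per arm (Sample size), 5% rejection level (Statistical analysis; sidedness not stated, two-sided assumed), four media and a ceiling of 300 colonies (Microbiological methods). Assumed, because the article gives no figures for colony counts: correlation r of 0 to 0.5 between pre-dressing and day-6 counts, and a day-6 difference of 0.4 SD as an illustration.

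**Step 1: the plan's own figure.** There is none for colonisation. The 100 per arm was derived for infection rates and does not bear on this point.

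**Step 2: the baseline test.** Among all randomised patients it rejects about 5% of the time whatever wear time does. Over four media, the chance of at least one significant result is 1 − 0.95⁴ = 18.5% if the media were independent, and less if their counts go together.

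**Step 3: what adjustment buys.** Residual variance is multiplied by 1 − r². The equivalent sample size per arm is 100/(1 − r²). Approximate power is Φ(0.4 × √(100/2) / √(1 − r²) − 1.96). At r = 0 this is Φ(2.83 − 1.96) = 81%.

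| r | 1 − r² | variance removed | equivalent n per arm | power |
|---|---|---|---|---|
| 0 | 1.00 | 0% | 100 | 81% |
| 0.2 | 0.96 | 4% | 104 | 82% |
| 0.3 | 0.91 | 9% | 110 | 84% |
| 0.5 | 0.75 | 25% | 133 | 90% |

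A simulation respecting the form of the data (2,000 trials per scenario, 100 per arm, log-normal-Poisson counts capped above 300) gave 77% power for the day-6 Mann-Whitney test at r = 0.2 and at r = 0.5. Rank ANCOVA on the pre-dressing count gave 78% and 85%.

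**Step 4: validity and chance imbalance.** With no wear-time effect, the day-6 Mann-Whitney test rejected in 4.4 to 5.8% of simulated trials, so its overall type I error is right. In those trials where the baseline test happened to be significant, it rejected in 3 to 10% at r = 0.2 and 12 to 17% at r = 0.5; rank ANCOVA rejected in 1 to 7%. These conditional rates rest on about 100 trials per scenario, so their standard errors are roughly 2 points near 5% (√(0.05 × 0.95/100)) and 4 points near 15% (√(0.15 × 0.85/100)).

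**Step 5: reading across the within-arm tests.** If both arms change equally and each test has power p, the chance that exactly one is significant is 2p(1 − p): 50% at p = 0.5, 32% at p = 0.8, 18% at p = 0.9 and 9.5% at p = 0.95. Thus 50% is the maximum. Simulating the planned Friedman and Wilcoxon tests with no difference between arms at day 6 and r of 0.2 and 0.5, they disagreed in 46 and 53% of trials at a common change of 0.25 SD, and in 21 and 6% at 0.5 SD.

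**The case against.** The case for leaving the plan alone is strong in several respects.

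- A reader might infer that wear time is not properly tested. The article does not support that: the day-6 Mann-Whitney test is a direct randomised comparison with correct overall size. Adjustment improves efficiency; it does not correct an error.
- A reader might infer that the within-arm tests are meant to demonstrate a wear-time effect. The article says nothing of the kind; it justifies them by a possible role of colonisation in infection. Misreading is a risk, not a plan.
- A reader might see inconsistency in using Friedman in one arm and Wilcoxon in the other. It follows from three samples against two; each is the matching paired rank test.
- The gain may be small. The pre-dressing swab comes after a chlorhexidine shower, alcoholic chlorhexidine antisepsis and saline cleansing, so counts may be low and carry little information, especially on the fungal and enterobacterial media.
- A pre-dressing difference need not be pure chance among those analysed. Under End points, group II patients whose dressings get wet before day 6 are withdrawn after allocation. If their samples are dropped, the difference could partly reflect selection.

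All five points stand, and they limit the weight of the concern. They do not remove it: the article names its tests, so the unadjusted comparison and the baseline test are stated choices rather than detail left to a fuller document. The withdrawal point does not give the baseline test a use either, since that test neither identifies nor corrects selection.

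**Conclusion.** The point holds as a free improvement of minor weight, confined to a secondary outcome. The planned day-6 test is valid. It forgoes a reduction in residual variance of about 0 to 25%, which under the 0.4 SD illustration moves power from 81% to between 81 and 90%, and it leaves the result exposed to chance baseline imbalance. The size depends entirely on the assumed r of 0 to 0.5; near zero, almost nothing is gained.

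On the within-arm tests the finding is a caution about interpretation only. Disagreement between them when the arms do not differ has probability 2p(1 − p) under equal power, at most 50% and much less when both tests have high power. The primary infection analysis is unaffected.

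**What to change.** For each medium, replace the two Mann-Whitney tests with one between-arm comparison of day-6 counts that includes the pre-dressing count on that medium: either rank ANCOVA, or a proportional-odds model with group and pre-dressing count. Counts over 300 form the top category, so the ceiling needs no further device. Choose one method in advance.

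Summarise pre-dressing counts by arm without a test. State that the conclusion on wear time comes from the between-arm model only. Keep the Friedman and Wilcoxon tests, labelled descriptive, with a sentence that significance in one arm and not the other is not evidence of a wear-time effect.

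The cost is wording: every sample needed is already scheduled, and Trial status describes recruitment as ongoing, so the change can be fixed before analysis. Adjustment does not repair the withdrawal of group II patients alone for wet dressings, which needs to be dealt with separately.
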